## Abstract

**Background:**

Cisplatin is a key drug in lung cancer therapy. However, cisplatin is also well known to induce gastrointestinal disorders, such as chemotherapy-induced nausea and vomiting, anorexia, and weight loss. These symptoms sometimes affect patients’ quality of life and make continuation of chemotherapy difficult. Anorexia is a cause of concern for patients with cancer because a persistent loss of appetite progresses to cancer cachexia. Although evidence-based management for chemotherapy has recently been established, there is room for improvement.

**Methods/design:**

This placebo-controlled, double-blind, randomized trial will aim to determine the efficacy of the traditional Japanese *Kampo* medicine *rikkunshito* (TJ-43) for preventing anorexia caused by cisplatin-including chemotherapy in patients with lung cancer. Patients with lung cancer who plan to receive cisplatin-including chemotherapy will be recruited. Patients who provide written consent will be randomly allocated to receive either TJ-43 (arm A) or placebo (arm B) for one course of chemotherapy (21 or 28 consecutive days). Investigators and patients will be masked to the treatment assignment throughout the trial. The primary endpoint will be evaluated as the change in dietary intake from day 0 (the day before the start of chemotherapy) to day 7 of cisplatin-including chemotherapy. The two arms of the trial will comprise 30 patients each. From November 2014, a total of 60 patients will be recruited, and recruitment for the study is planned to be complete by October 2017.

**Discussion:**

This trial is designed to examine the efficacy of *rikkunshito* (TJ-43) for reducing anorexia and maintaining food intake caused by cisplatin-including chemotherapy in patients with lung cancer.

**Trial registration:**

Japan Pharmaceutical Information Center Clinical Trials Information (JAPIC CTI), trial registration: JAPIC CTI-142747. Registered on 15 December 2014; the RICH trial.

**Electronic supplementary material:**

The online version of this article (doi:10.1186/s13063-017-2227-6) contains supplementary material, which is available to authorized users.

## Background

Cisplatin is a key drug in lung cancer chemotherapy. However, cisplatin is also well known to induce gastrointestinal disorders, such as chemotherapy-induced nausea and vomiting (CINV), anorexia, and weight loss. These symptoms sometimes affect patients’ quality of life (QOL) and make continuation of chemotherapy difficult. Although the mechanism of chemotherapy-induced appetite loss is not thoroughly understood, cisplatin-related acute gastrointestinal disorders reportedly involve secretion of serotonin (5-hydroxytryptamine, 5-HT) from enterochromaffin cells. Therefore, 5-HT3 receptor antagonists are widely used to prevent cisplatin-induced nausea and vomiting [1]. Evidence-based CINV management has recently been established by several societies, including the National Comprehensive Cancer Network [2], American Society of Clinical Oncology [3], and Multinational Association of Supportive Care in Cancer/European Society for Medical Oncology [4]. Furthermore, since guidelines for the proper use of antiemetics were announced by the Japan Society of Clinical Oncology in May 2010 [5], the management of CINV in Japan has steadily improved [6]. According to the above guidelines, cisplatin is classified as highly emetogenic chemotherapy (HEC), and the standard prophylaxis for CINV is a three-drug combination of a 5-HT3 receptor antagonist, neurokinin-1 receptor antagonist, and dexamethasone. In addition, a phase III randomized controlled trial [7], which formed the basis of the current standard supportive care for HEC, reported an approximately 80% complete remission rate of acute-onset CINV (≤24 h after anti-cancer agent administration) and a 60 to 70% complete remission rate of late-onset CINV (24–120 h after anti-cancer agent administration).

The above-mentioned antiemetic agents that have been introduced as treatment for CINV have led to improvements in CINV management. However, there is room for further improvement in the management of chemotherapy, especially HEC. Anorexia is a cause of concern for patients with cancer because a persistent loss of appetite progresses to cancer cachexia. In patients treated with cisplatin, anorexia is thought to be caused not only by CINV but also by changes in ghrelin dynamics. Ghrelin is an intense appetite-enhancing hormone comprising 28 amino acids and is secreted mainly from the stomach. The plasma ghrelin concentration is thought to be related to gastrointestinal disorders [8].

*Kampo* medicines are produced uniquely in Japan and have been approved by the Ministry of Health, Labor and Welfare of Japan for treatment of numerous diseases. *Rikkunshito* (TJ-43) is a traditional Japanese *Kampo* medicine that has been prescribed to treat upper gastrointestinal symptoms such as appetite loss and nausea. It comprises eight herbal components, containing a dried extract of the following: 19% *Atractylodes lancea* rhizome, 19% ginseng (*Ginseng radix*), 19% *Pinellia* tuber (*Pinellia ternata*), 19% *Poria sclerotium* (hoelen), 9% jujube (*Ziziphus fructus*), 9% *Citrus unshiu* peel (*Aurantii nobilis pericarpium*), 5% glycyrrhiza (*Glycyrrhizae radix*), and 2% ginger (*Zingiber* rhizome).

Previous studies have reported that TJ-43 enhances digestive tract motility [9], improves the gastric accommodation reflex [10], protects against gastric mucosal injury [11], and enhances appetite [12]. Based on these mechanisms, TJ-43 has been used to treat various gastrointestinal tract diseases, such as functional dyspepsia [13], gastroesophageal reflux disease [14], and chemotherapy-induced nausea [15].

We previously conducted a retrospective analysis of the efficacy of TJ-43 for preventing CINV and maintaining food intake in patients with lung cancer treated with cisplatin-based chemotherapy (presented at the 113rd Annual Meeting of the Japan Surgical Society, not published). Patients receiving chemotherapy for treatment of lung cancer were divided into those using only conventional antiemetic agents and those receiving chemotherapy to which TJ-43 was added. We showed that the rate of late-onset CINV as assessed by the Multinational Association of Supportive Care in Cancer questionnaire [16] was 76% in patients receiving TJ-43 and 40% in patients not receiving TJ-43. In addition, the average dietary intake rate from day 1 (the start date of chemotherapy) to day 5 was 72.2 ± 18.1% (mean ± standard deviation) in patients receiving TJ-43 and 58.4 ± 18.2% in patients not receiving TJ-43.

We are, therefore, conducting a placebo-controlled, double-blind, randomized trial to evaluate the efficacy of TJ-43 for chemotherapy-induced anorexia (RICH trial). We herein report the details of the trial design. This trial will be carried out in compliance with the ordinance of the Ministry of Health, Labor and Welfare in Japan, Good Post-Marketing Study Practice, Good Clinical Practice, and the guideline for clinical trials “Statistical Principles for Clinical Trials” [17]. This trial was also planned with reference to “Structure and Content of Clinical Study Reports” [18].

## Methods/design

### Objectives

The RICH trial is a placebo-controlled, double-blind, randomized trial that aims to examine the efficacy of TJ-43 for anorexia and maintaining food intake in patients with lung cancer who plan to receive cisplatin-including chemotherapy. The Standard Protocol Items: Recommendations for Interventional Trials (SPIRIT) Figure is shown in Fig. 1.

**Fig. 1 Fig1:**
[figure not shown]
Summary of enrollment, interventions, assessments, and timing for measurements (Standard Protocol Items: Recommendations for Interventional Trials (SPIRIT) Figure)

### Endpoints

#### Primary endpoint

The primary endpoint is:Change in dietary intake from day 0 (the day before the start of chemotherapy) to day 7 of chemotherapy

#### Secondary endpoints

The secondary endpoints are:Changes in QOL assessment (QLQ-C30 [19] + QLQ-LC13 [20]) at days 0, 7, and 22 or 29 (the start date of the next chemotherapy course)The incidence of any adverse events, except anorexiaThe proportion of patients who receive dose-reduced cisplatin-including chemotherapy in the next courseThe proportion of patients who delay the start of cisplatin-including chemotherapy in the next courseThe proportion of patients requiring extended hospitalizationChanges in nutritional indices (total protein and albumin concentrations) at days 1, 7, and 22 or 29 (the start date of the next chemotherapy course)

#### Other outcome measures

Other outcome measures are:Changes in plasma metabolite concentrations at days 1, 7, and 22 or 29 (the start date of the next chemotherapy course)

### Eligibility criteria

#### Inclusion criteria

The inclusion criteria are:Patients with a histologically or cytologically confirmed diagnosis of lung cancerPatients planning to receive cisplatin-including chemotherapyPatients capable of oral ingestion of medicineAdequate function of vital organs and bone marrowAge of 20 years or older at the time of registrationEastern Cooperative Oncology Group performance status of 0 or 1Written informed consent provided to participate in the study

#### Exclusion criteria

The exclusion criteria are:The use of any *Kampo* medicines within 2 weeks before registrationHemoptysis (> 2.5 mL/day) within 2 weeks before registrationPeripheral neuropathy of grade > 1 (National Cancer Institute Common Terminology Criteria for Adverse Events version 4.0)Brain metastasisPregnant or lactating womenCurrent treatment with cisplatin-including chemotherapyPatients scheduled to receive cisplatin (≤ 20 mg/m^2^)Serious infectionSevere complications (e.g., cardiac disease, interstitial pneumonia, uncontrolled diabetes mellitus)Uncontrolled pleural effusion, ascites or pericardial effusionOther active malignanciesHistory of severe drug allergyAny other medical condition that makes the patient unsuitable for inclusion in the study, according to the opinion of the investigator

### Registration

An eligibility report form will be sent to the Registration Center at Tsumura & Co. (Tokyo, Japan). Patients who meet all eligibility criteria will be randomly allocated to receive either TJ-43 (arm A) or placebo (arm B) at the individual institutions. Each participant must be hospitalized to receive chemotherapy. The placebo is indistinguishable from the TJ-43 in appearance. Investigators prescribing either TJ-43 or placebo to each patient will not know which patient is allocated to which arm.

Patients and investigators (including the investigators assessing blood tests) will be masked to the treatment assignment throughout the study. Each arm will comprise 30 patients. Recruitment began in November 2014 and will end in October 2017 or until 60 participants have been recruited.

This trial is being conducted at two institutions in Fukushima prefecture of Japan.

### Treatment methods

#### Study drug

The study drug (TSUMURA *Rikkunshito* Extract Granules for Ethical Use or placebo) will be administered at a dose of 2.5 g three times per day (total daily dose of 7.5 g). The placebo formulation matches that of TJ-43 in terms of appearance and texture. TJ-43 and the matching placebo were manufactured by Tsumura & Co. (Tokyo, Japan).

#### Arm A (TJ-43 group) and arm B (placebo group)

TJ-43 (arm A) or placebo (arm B) will be administered per os at a dose of 2.5 g three times per day (total daily dose of 7.5 g), either before meals or between meals, for one course of chemotherapy (21 or 28 consecutive days). The study drug will be initiated on the first day of chemotherapy (day 1) and continued until the day before the start of the next course of chemotherapy (day 22 or 29; allowable range of + 7 days) (Fig. 2). If the timing of the next chemotherapy administration is postponed, the investigators will continue to administer the study drug for the extended period.

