### Randomization and blinding

The participants will be assigned to either the TJ-43 group or the placebo group in a 1:1 ratio using a block randomization method. A randomization list has been pregenerated, and this assignment list will be kept in a safe until unblinding. The randomization list will not be disclosed to the investigators. The placebo drug is indistinguishable from TJ-43 in appearance. Therefore, both the investigators and participants will be blinded to the treatment group throughout the study. Unblinding will take place only after the trial is finished and data are fixed, except in the case of emergencies.

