### Data collection

After registration and assignment to treatments, prospective data will be collected for all patients, including sex, date of birth, physical findings, and clinical information (such as medical history, complications, and regimen of lung cancer chemotherapy). The investigators will measure the patients’ dietary intake during each meal from day 0 (the day before the start of chemotherapy) to day 7. For each meal, the weight of food (including tableware) before and after the meal will be measured. Dietary intake will be calculated by subtracting the weight of food consumed (including tableware) after the meal from that of food (including tableware) before the meal. The investigators will also check meals other than hospital diets.

In addition, the investigators will check changes in the patients’ QOL assessment at days 0, 7, and 22 or 29 (the start date of the next chemotherapy course), the incidence of any adverse events except anorexia, the proportion of patients who received dose-reduced cisplatin-including chemotherapy in the next course, the proportion of patients who delayed the start of cisplatin-including chemotherapy in the next course, and the proportion of patients requiring extended hospitalization.

Blood samples will be routinely collected at days 1, 7, and 22 or 29. Two sets of specimens will be drawn: routine monitoring samples and trial samples. Possible side effects, such as neutropenia and renal dysfunction, will be checked in both groups. The routine blood samples will undergo measurements of the hemoglobin concentration; leukocyte, neutrophil, and platelet counts; and urea nitrogen and creatinine concentrations. These parameters will be used to manage the side effects of lung cancer treatment in daily clinical practice.

Possible side effects in the TJ-43 group also include liver dysfunction, myopathy, hypersensitivity, and electrolyte abnormalities. The trial blood samples will be collected not only to examine safety (liver enzyme, creatinine phosphokinase, and electrolyte concentrations) but also to examine nutritional indices (total protein and albumin concentrations).

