### Sample size

The sample size was calculated based on our retrospective data showing that the average dietary intake rate from day 1 to 5 was 72.2% ± 18.1% (mean ± standard deviation) in patients administered TJ-43 and 58.4% ± 18.2% in patients who were not administered TJ-43 (unpublished data). Based on this preliminary study, we calculated that 28 patients per group would be required to achieve a power of 80% with a two-sided significance level of *p* < 0.05 for detecting the superiority of concomitant treatment with TJ-43 by a *t* test. Here, the assumed effect size (*d*) was 0.76. To account for possible dropouts (10%), the target number of patients was, therefore, set at 30 per group (60 in total) (see Additional file 1).

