### Study design and statistical analysis

The effects of TJ-43 against chemotherapy-induced anorexia have yet to be determined. The RICH trial is designed to evaluate the efficacy of TJ-43 for anorexia in patients with lung cancer undergoing treatment with cisplatin-including chemotherapy. It is a placebo-controlled, double-blind, randomized trial that will be conducted at two institutions.

The primary endpoint will be the change in dietary intake from day 0 (the day before the start of chemotherapy) to day 7. The mean dietary intake in hospital (MDIH) is defined as the total hospital diet intake divided by the number of records. The investigators will calculate the MDIH each day from day 0 through day 7 for each patient, and the value at day 0 will be used as the baseline. The primary endpoint variable of this trial is the mean change in the MDIH from the baseline, averaged from day 1 through day 7. This will be evaluated by analysis of covariance (ANCOVA), which employs the baseline value as the covariate, to estimate the difference between the two treatment groups (*n* = 30 per group). Additionally, for ease of interpretation, the time profile of MDIH from day 1 through day 7 will be analyzed by a linear mixed-effects model using the baseline value as the covariate.

The secondary endpoints, namely the changes in nutritional indices (total protein and albumin concentrations), will also be analyzed by ANCOVA, which employs the baseline value (day 1) as the covariate. The changes in QOL assessment (QLQ-C30, QLQ-LC13) will be analyzed by ANCOVA for each item, which employs the baseline value (day 0) as the covariate. Items in the QOL assessment include the evaluation of nausea, vomiting, and anorexia. In addition, the proportion of patients who receive dose-reduced or delayed chemotherapy and the proportion of patients requiring extended hospitalization will be compared between the two treatment groups using the chi-square test or Fisher’s exact test. The incidence of adverse event will be compared by means of Fisher’s exact test.

The analyses of efficacy outcomes will be performed in the full analysis set. An interim analysis will not be performed.

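### The primary model adjusts only for day 0 intake and omits the planned cisplatin regimen: a modest loss of precision, not a bias

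*Protocol article*

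**What the plan says.** **Background chemotherapy.** Inclusion criteria require planned cisplatin-containing chemotherapy. Exclusion criteria remove patients whose scheduled cisplatin is 20 mg/m2 or less. The article gives no list of regimens and no upper dose. Under Arm A (TJ-43 group) and arm B (placebo group) the study drug is given "for one course of chemotherapy (21 or 28 consecutive days"). Data collection lists the "regimen of lung cancer chemotherapy" among the items recorded.

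**Allocation.** Under Randomization and blinding, patients are assigned "in a 1:1 ratio using a block randomization method". The Registration section adds that this happens at the individual institutions. No stratification factor is named.

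**Analysis.** Under Study design and statistical analysis, the primary variable is the mean change in MDIH from day 0, averaged over days 1 to 7. It is tested by "analysis of covariance (ANCOVA), which employs the baseline value as the covariate". The mixed model for the daily profile uses the same single covariate. The QOL and nutrition ANCOVAs also adjust only for their own baseline (day 0 and day 1), with the last assessment at day 22 or day 29. Regimen, dose and course length enter no stated analysis.

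**The concern.** The trial measures loss of intake caused by chemotherapy, so the planned chemotherapy is an obvious candidate prognostic factor. It is also known early, because the scheduled cisplatin dose has to be checked for eligibility. Baseline intake cannot stand in for it: it is measured the day before chemotherapy starts and carries no information on how strongly the coming regimen will suppress eating.

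Two things are at stake for the primary endpoint. Variance that regimen could explain stays in the error term. And if the arms happen to differ in regimen, the estimate in that realised trial is shifted, and no stated analysis would show it.

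The final visit raises a separate point. QOL, total protein and albumin are taken at day 22 in some patients and at day 29 in others, according to course length, and are analysed together with no term for that difference.

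**Working it through.** **Inputs from the protocol (Sample size).** Intake was "72.2% ± 18.1% (mean ± standard deviation) in patients administered TJ-43" and 58.4% ± 18.2% without it; the target is "a power of 80% with a two-sided significance level of *p* < 0.05"; "the assumed effect size (*d*) was 0.76"; 28 per group, raised to 30.

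**Reproducing the plan's figure.** The difference is 72.2 − 58.4 = 13.8 points and the pooled SD is √((18.1² + 18.2²)/2) = 18.15, so d = 13.8/18.15 = 0.76. The normal approximation gives n = 2(1.960 + 0.842)²/0.76² = 27.2, hence 28 per group, as stated. The exact t test needs 28.17, hence 29. Exact power is 79.8% at 28 per group and 82.5% at 30.

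**Assumed inputs (not in the documents).** Regimen is treated as a two-level factor. The heavier level applies to 30% or 50% of patients and lowers intake by g = 0.3, 0.5, 0.8 or 1.0 SD. On the SD of 18.15 that is 5.4, 9.1, 14.5 or 18.2 points.

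**Chance of imbalance.** With X₁ and X₂ independent Binomial(30, p), P(|X₁ − X₂| ≥ 6), a gap of 20 points or more, is 12.0% at p = 0.3 and 15.5% at p = 0.5. By symmetry half of this favours TJ-43: 6.0% and 7.75%. A gap of 9 or more (30 points) has probability 1.6% and 2.7%.

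**Consequences.** 40,000 simulated trials per scenario, 30 per arm, total SD fixed at 1, with and without the regimen covariate. Day 0 intake was not simulated; d = 0.76 is taken as the effect on the analysis scale. Each cell gives p = 0.3 / p = 0.5.

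| Regimen effect | Shift when a gap ≥ 20 points favours TJ-43 (points of intake) | Rejection under no drug effect, given a gap ≥ 20 points: without covariate | Same, with covariate | Power at d = 0.76: without | Power: with |
|---|---|---|---|---|---|
| 0.3 SD | 1.2 / 1.4 | 5.7% / 5.9% | 5.2% / 5.2% | 82.8% / 82.5% | 82.8% / 82.6% |
| 0.5 SD | 2.2 / 2.3 | 6.8% / 7.3% | 4.6% / 5.3% | 82.7% / 82.8% | 84.0% / 84.3% |
| 0.8 SD | 3.3 / 3.4 | 9.4% / 9.0% | 4.9% / 4.7% | 82.4% / 82.6% | 87.0% / 88.0% |
| 1.0 SD | 4.2 / 4.4 | 12.1% / 12.7% | 4.8% / 4.9% | 82.9% / 82.3% | 89.8% / 91.2% |

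Averaged over all randomisations, rejection under no drug effect is 4.8% to 5.1% without the covariate and 4.8% to 5.1% with it.

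**Cross-check by formula.** Regimen explains R² = p(1 − p)g² of the variance, and the effective effect size becomes 0.76/√(1 − R²). At p = 0.5, g = 1.0: R² = 0.25, effect size 0.76/0.866 = 0.878, n = 15.70/0.878² = 20.4, hence 21 per group in place of 28, and exact power at 30 is 91.7%. At p = 0.3, g = 0.3: R² = 0.0189, n = 27, power 83.2%.

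**The case against.** **There is no error to repair.** Block allocation followed by ANCOVA on baseline is coherent, and any prognostic factor left out of a model can be imbalanced by chance. This stands. A reader might infer that an imbalance in emetogenic load would pass as a drug effect and raise the false-positive rate. The calculations do not support that: the nominal 5% already averages over lucky and unlucky allocations. The excess appears only conditionally on an imbalance.

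**The allocation may already use regimen.** The article condenses a full protocol that is not shown, and strata may be named there. A reader might infer that allocation ignores regimen; the article does not establish this. The point rests only on the stated covariates.

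**Course length cannot affect a day 1 to 7 endpoint.** Correct. For the primary variable, 21 against 28 days could matter only as a marker of regimen, and the documents do not say that it is one. It has no place in the primary model. At the final visit it bears directly on timing, though imperfectly: that visit is tied to the start of the next course, for which the protocol allows 7 further days and possible postponement.

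**The background is not unlimited.** Cisplatin as a whole is classed as highly emetogenic, low scheduled doses are excluded, and both arms receive the same antiemetics. That narrows the likely regimen effect but does not show that intake is equal across doses and partner drugs.

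**The size is assumed.** True. Regimen effects of 0.8 and 1.0 SD exceed the whole assumed drug effect of 0.76 SD. At 0.3 to 0.5 SD the gain is only about 0 to 1.5 points of power.

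**Conclusion.** The point holds as a modest matter of precision and robustness. The stated primary ANCOVA and mixed model omit a pre-treatment factor that the trial records and that day 0 intake cannot represent. The estimate is not biased and overall type I error is not inflated.

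The loss is about 0 to 9 points of power at 30 per arm. If a gap of 20 points or more favours TJ-43, the estimate also shifts by about 1 to 4 points of intake, against a planned difference of 13.8. Both ranges rest on an assumed regimen effect of 0.3 to 1.0 SD and an assumed prevalence of 30% to 50%; the documents give neither. The lower end is negligible.

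What makes it worth acting on is the low cost, and that the same adjustment chosen after unblinding would look driven by the data. For the final-visit QOL and nutrition models, the reason to include planned course length is direct, because values planned a week apart are pooled.

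**What to change.** Before unblinding:

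- Add planned cisplatin dose (mg/m2) or a prespecified regimen group, as scheduled at registration, as a covariate in the primary ANCOVA and in the mixed model for days 1 to 7.
- Add planned course length (21 v 28 days) to the QOL and nutrition ANCOVAs at the final visit only.
- Use planned values throughout. Delivered dose and actual course length arise after randomisation, and dose reduction and delay in the next course are themselves secondary endpoints.

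The cost is one or two degrees of freedom in the primary model, out of 60 − 3 = 57 (intercept, arm, baseline). No extra patients and no change to eligibility or chemotherapy are needed. One practical check: the article says that the regimen is recorded, not that the scheduled mg/m2 is. Confirm that the dose can be taken from the eligibility report form, where the 20 mg/m2 exclusion has to be verified; if it cannot, use regimen group.
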